### **DATA ANALYSIS**

For the descriptive analysis of the data, normality will be checked using the Kolmogorov-Smirnov and Shapiro-Wilk tests (for  $n < 30$ ). Variables with a normal distribution will be described by mean, standard deviation, and value range, while variables that do not follow a normal distribution will be described using the median and interquartile range. Qualitative variables will be presented as frequencies and percentages.

Regarding quantitative analysis, a correlation analysis (Pearson correlation coefficient) will be performed to demonstrate the validity of the evaluation procedure selected for our study. Cronbach's alpha coefficient will be used to demonstrate its reliability. For comparing two means, inferential statistical analysis will use the Student's t-test (parametric method for independent samples), the Mann-Whitney U test (non-parametric test for two independent samples), and the Wilcoxon test (non-parametric test for repeated measures). The comparison of three or more means will be analyzed using: ANOVA (for independent groups using Snedecor's F -ANOVA-) and Kruskal-Wallis (non-parametric method using the H test). For repeated measures, Snedecor's F test will be used in parametric testing and Friedman's test in non-parametric testing. Correlations will be performed using two methods: Pearson correlation (for normally distributed variables) or Spearman correlation (for non-normally distributed variables). A multivariate logistic regression analysis will be performed to determine variables associated with events of interest. In the logistic regression model, variables that were significant in the bivariate analysis or those relevant to the study will be included. For qualitative or categorical variables, contingency tables and the Chi-Square significance test will be used for two independent samples.

P-values less than 0.05 will be considered significant, that is, with a 95% confidence interval. IBM SPSS Statistics version 28.0.1 will be used for the statistical analysis.

The statistical analysis will be conducted by intention-to-treat. Population characteristics will be presented as means and standard deviations for continuous variables and as frequency distributions for qualitative variables. To evaluate comparability at baseline between the two study groups, the Chi-Square test will be used for qualitative variables, and the Student's t-test will be used for comparing means between the two groups. The effect of the intervention on the study variables will be assessed using a repeated measures ANOVA with two study factors (time \* group). Subgroup analyses will be performed considering certain baseline evaluation variables and/or categories, such as age or initial score on the FACT scale. Hypothesis testing will have an alpha risk of 0.05 as the statistical significance threshold. The statistical software used will be SPSS, version 23.0.

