#### **WITHDRAWAL CRITERIA:**

- Patient's death.
- Disease progression leading to a terminal state.
- Hospitalization at the time of home follow-up.
- Incomplete final assessment.

**Randomization:** Patients in the study population, after the initial interview with the research team and having met the selection criteria, will be randomly assigned to two groups: an intervention group (IG) and a control group (CG). The allocation sequence will be generated by

an independent researcher using the Epidat 4.2 software, with a 1:1 ratio. Participants will be randomized based on the order of their baseline assessment, and the randomization sequence will remain concealed until each patient is assigned to the appropriate group.

**Blinding:** The sequence, randomization, recruitment, and assignment work for each group (experimental or control) will be completed by research staff not involved in the evaluations or interventions, preventing potential biases in the study. Participants will also be blinded and unaware of the group to which they are assigned and the intervention they will receive. External research personnel trained in evaluation procedures will be incorporated to minimize any contamination between groups, ensuring third-party blind assessment. Additionally, the researchers responsible for the statistical analysis will be blinded, increasing the scientific rigor and quality of the study.

**Sample size:** The sample size estimation is based on the potential modification of one of the study's primary variables, the Barthel Index score. A pilot study with a similar population was used as a reference, where the Barthel Index score changed by 5.8 points. With these premises, accepting an alpha risk of 0.05 and a beta risk of 0.2 in a bilateral contrast, 40 subjects in each group are required to detect a difference of at least 5.8 units. A common standard deviation of 8.7 is assumed. A follow-up loss rate of 10% has been estimated. The sample size calculation was performed with the EPIDAT 4.2 software.

---

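### The protocol's non-parametric option for repeated measures (Friedman, Wilcoxon) cannot compare the arms, and it is not reconciled with the unconditional time-by-group ANOVA given for the intervention effect

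*Protocol*

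**What the plan says.** The protocol describes the analysis of three-visit data (baseline, 15 days, 1 month) in two ways.

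- **First part of Data analysis.** It says "normality will be checked using the Kolmogorov-Smirnov and Shapiro-Wilk tests". The sentence is introduced as part of the descriptive analysis, and its stated consequence is mean and SD versus median and interquartile range. The text then lists parametric and non-parametric tests: Student's t, Mann-Whitney and Wilcoxon for two means; ANOVA and Kruskal-Wallis for three or more. Then: "For repeated measures, Snedecor's F test will be used in parametric testing and Friedman's test in non-parametric testing". Wilcoxon is labelled as the repeated-measures test and Mann-Whitney as the test for two independent samples. Normality is explicitly tied to a choice of method only for Pearson versus Spearman correlation.
- **Second part of Data analysis, repeated under Statistical analysis.** It says "The effect of the intervention on the study variables will be assessed using a repeated measures ANOVA with two study factors", the factors being time and group. No normality condition is attached.

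The two parts also differ on the SPSS version (28.0.1 and 23.0) and on descriptive summaries (median and interquartile range for non-normal variables, against mean and SD for all continuous variables).

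**The concern.** Friedman's test and the Wilcoxon signed-rank test ask whether scores change over time in one set of patients. The trial asks whether Barthel changes more in the experimental arm than in the control arm. Patients enter just before hospital discharge, so some change in both arms is plausible, and a within-patient test would respond to it.

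The first part of the section therefore offers, for repeated measures, a non-parametric option that is no counterpart to the time-by-group test in the second part. No sentence says which part governs. An analyst who reads the pairing of tests as a normality-based switch could reach Friedman or Wilcoxon for the primary outcome and report a within-arm improvement where a randomised comparison was intended.

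**Working it through.** **1. The plan's own sample size.** The Sample size paragraph gives "accepting an alpha risk of 0.05 and a beta risk of 0.2 in a bilateral contrast", "A common standard deviation of 8.7 is assumed" and "A follow-up loss rate of 10% has been estimated", and concludes that "40 subjects in each group are required to detect a difference of at least 5.8 units".

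n per arm = 2 × (1.96 + 0.842)² × (8.7 / 5.8)² = 2 × 7.85 × 2.25 = 35.3, so 36. Allowing for 10% loss: 36 / 0.9 = 40. The stated figure is reproduced, and about 36 per arm are expected at the end.

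**2. What each test detects.** Simulation: two arms of 36, three visits, SD 8.7, scores rounded to 5-point steps, within-patient correlation 0.5 or 0.7. The step and the correlations are assumptions. Both arms gain 5.8 points by 1 month, so the true arm difference is zero.

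| Test at the 5% level | Significant, correlation 0.5 | Significant, correlation 0.7 |
|---|---|---|
| Friedman, arms pooled | 99.5% | 100% |
| Friedman, within an arm | 87-89% | 98% |
| Wilcoxon, within an arm | 96% | 99.9% |
| Mann-Whitney on change | 4.4% | 4.8% |
| Time-by-group ANOVA | 4.3% | 4.1% |

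A repeat run gave the same picture: pooled Friedman 99-100%, within-arm Wilcoxon 96% or more, between-arm tests 5-6%. Friedman and Wilcoxon carry no information on the arm difference.

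**3. Would Barthel fail a normality test, if one steered the choice?** The protocol gives Barthel items of 0 to 15 and a total of 0 to 100; it does not state a 5-point step. With that step assumed and a normal underlying score, samples of 36 are rejected as follows.

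| SD | K-S with Lilliefors correction | Shapiro-Wilk | K-S uncorrected |
|---|---|---|---|
| 8.7 | 70% | 36% | 4% |
| 12 | 41% | 16% | 1% |
| 15 | 26% | 10% | 0.2% |
| 20 | 16% | 7% | 0.1% |

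Without rounding, the Lilliefors rate at SD 8.7 is about 5%. Coarse scoring alone can cause rejection, but how often depends on the SD and on the version of the test.

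**4. Power of a single between-arm analysis.** True difference 5.8 at 1 month, 36 per arm, SD 8.7 read as the between-patient SD at a visit.

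For a linear model adjusted for baseline, the residual SD is 8.7 × √(1 − r²).
- r = 0.5: residual SD 7.53; SE = 7.53 × √(2/36) = 1.78; 5.8 / 1.78 = 3.27; power ≈ Φ(3.27 − 1.96) = 90%.
- r = 0.7: residual SD 6.21; SE = 1.46; 5.8 / 1.46 = 3.96; power ≈ Φ(3.96 − 1.96) = 98%.

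Rounding to 5 points and using the t distribution lower these slightly.

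| Simulated power | r = 0.5 | r = 0.7 |
|---|---|---|
| Time-by-group ANOVA, three visits | 68% | 88% |
| Mann-Whitney on change | 74% | 92% |
| Linear model adjusted for baseline | 88% | 96% |

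**The case against.** The strongest reply is that a valid between-arm analysis is already fixed, and stated twice. The time-by-group ANOVA carries no normality condition, and a specific rule for the intervention effect would normally override a general list of methods. The list never assigns Friedman or Wilcoxon to Barthel or to the intervention effect, and it includes Mann-Whitney, which does compare the arms and can be applied to change scores. Test selection is also often left to a statistical analysis plan, which is not available here. Much of this stands and limits the point. It does not remove the point, because the two parts of the protocol describe the same data differently and nothing says which one governs.

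A reader might infer four stronger things that the documents do not support.

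- **That a normality pre-test chooses the treatment comparison.** The check is written for the descriptive analysis and selects a method explicitly only for correlations. For the other tests this is a natural reading, not a stated rule.
- **That Barthel will usually fail the check.** This needs the assumed 5-point step, an SD near 8.7 and the Lilliefors correction, which the protocol does not specify. Eligibility limits Barthel to 20-55 at baseline only, so rejection rates for baseline scores do not carry over to later visits.
- **That the non-parametric route is the likely one.** Nothing in the protocol makes it so.
- **That the 5% error rate is unprotected.** The two-stage procedure was not evaluated, and each between-arm test alone stays near 5%.

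**Conclusion.** The point holds in a limited form. The repeated-measures non-parametric option has no group factor and cannot serve as evidence of efficacy, and it conflicts with the unconditional time-by-group ANOVA. The first statement follows from what the tests are. The simulation shows its size: near-certain significance with no arm difference when both arms gain 5.8 points.

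The choice by normality is implied only. If it were applied, rejection from coarse scoring ranges from about 70% of samples of 36 (SD 8.7, Lilliefors) down to 4% (SD 8.7, uncorrected) or 16% (SD 20, Lilliefors).

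The power gain from baseline adjustment rests on SD 8.7 at each visit, 36 per arm, equal within-patient correlation of 0.5 or 0.7, and no truncation of baseline scores. The protocol does not say whether 8.7 is the SD of a score or of a change; under the other reading the power figures would shift.

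**What to change.** Merge the two parts of Data analysis with Statistical analysis so that they give one instruction:

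1. Name one between-arm primary analysis for Barthel at 1 month, applied whatever a normality test shows. A linear model with arm and baseline Barthel is preferable, reporting the difference in Barthel points with a 95% confidence interval.
2. Keep Mann-Whitney as a sensitivity analysis.
3. State that Friedman and Wilcoxon describe change within an arm and are not evidence of efficacy.
4. Confine the normality check to descriptive summaries and the choice of correlation coefficient, as written now.
5. Align the SPSS version and the rule for descriptive summaries in the same edit.

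An ordinal model for the five-level mMRC dyspnea scale is an option but is not needed to resolve this point. The change is wording only: it needs no new data, visits or patients, and the methods are in standard software.

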### Description of the variables

**Primary outcome variable: Activities of Daily Living (ADL):** ADLs will be assessed using the Barthel Index (BI), whose version has been translated and validated into Spanish (36). The scale assigns a score based on the degree of dependency for performing a series of basic activities, with each item scored between 0 and 15 points. The global range can vary between 0 (completely dependent) and 100 points (completely independent).

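### The supplementary logistic model admits covariates because they were significant in bivariate tests, in about 72 to 80 patients, so its odds ratios and p-values ignore the selection

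*Protocol*

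**What the plan says.** The Data Analysis section of the protocol announces the model and its purpose: "A multivariate logistic regression analysis will be performed to determine variables associated with events of interest". It then gives the entry rule: "In the logistic regression model, variables that were significant in the bivariate analysis or those relevant to the study will be included". A variable can therefore enter by either of two routes, a significant bivariate test or a judgement that it is relevant. The only threshold in the section is "P-values less than 0.05 will be considered significant". The event is not named and no variables are listed for the second route.

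The sample comes from the Sample size paragraph of Material and Methods: "40 subjects in each group are required to detect a difference of at least 5.8 units", with "A common standard deviation of 8.7 is assumed" and "A follow-up loss rate of 10% has been estimated".

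The effect of the intervention is assessed elsewhere. The closing paragraph of Data Analysis and the later Statistical Analysis section both assign it to a repeated measures ANOVA with time and group as factors.

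**The concern.** The protocol itself fixes the selection rule, so this is not a detail left open for a statistical analysis plan. A plan that dropped the screen would depart from the protocol.

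Screening on significance has two consequences. First, a null variable that passes by chance is carried into the multivariable model, where it is tested again on the same data and usually still looks significant. Second, a real predictor tends to pass when its estimate happens to be large, so the odds ratio reported after the screen is too far from 1. Ordinary p-values and confidence intervals from the final model reflect neither effect.

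What is at stake is the model's stated purpose, which is to find variables associated with events. A published list of predictors could contain false ones, and the real ones could be overstated.

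**Working it through.** **1. The protocol's sample size.** Inputs from the Sample size paragraph: difference 5.8, SD 8.7, two-sided alpha 0.05, power 0.80, loss 10%.

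n per group = 2 × (1.960 + 0.842)² × 8.7² / 5.8² = 2 × 7.85 × 2.25 = 35.3, rounded up to 36. Allowing for loss, 36 / 0.90 = 40. The stated 40 per group is reproduced. The model would therefore be fitted to between 2 × 36 = 72 and 2 × 40 = 80 patients.

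**2. Assumptions.** The protocol gives no event rate, number of candidates or true odds ratio. Steps 4 and 5 assume 72 patients, 50% events and independent standard-normal candidates, screened by t-test at p < 0.05 and then fitted together by logistic regression on the same data. The baseline visit records sociodemographic data, medical history, comorbidities and medications, plus the Barthel and six secondary scales, so 8 to 15 candidates is a plausible range.

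**3. Chance that at least one null candidate passes the screen.** For k independent candidates this is 1 − 0.95^k:
- k = 8: 34%
- k = 12: 46%
- k = 15: 54%

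**4. Chance that at least one null candidate is significant in the fitted model.** Simulation, 2,000 data sets per setting; ranges are across repeated runs.

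| Null candidates | Screened, then fitted | All entered, no screen |
|---|---|---|
| 8 | 30% | 35–36% |
| 12 | 39–42% | 49–50% |
| 15 | 46–49% | 61–63% |
| 5, fixed list | – | about 22% |

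With event rates of 20 to 50%, 72 or 80 patients, and 10 or 15 candidates, the screened figure stays between 33 and 49%.

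**5. One true predictor among 12 candidates.** True log odds ratio 0.40 per SD, so the odds ratio is exp(0.40) = 1.49.
- Screened: kept in 35 to 37% of trials. Mean log odds ratio when kept is about 0.71, an odds ratio of exp(0.71) = 2.03. Inflation on the log scale is 0.71 / 0.40 = 1.8-fold.
- Fixed five-covariate model, every estimate reported: mean log odds ratio about 0.46, an odds ratio of exp(0.46) = 1.58. The remaining excess over 0.40 is ordinary small-sample bias.
- Fixed five-covariate model, looking only at significant results: significant in 35 to 37% of trials, with a mean of about 0.77 when significant.

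**6. Events available.** At 20% events, 72 × 0.20 = 14.4; at 50%, 80 × 0.50 = 40. Ten candidates then have 1.4 to 4.0 events each. Five covariates have 2.9 to 8.0.

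**The case against.** Several points on the other side are sound and limit the finding.

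- **Significance is not the only way in.** Variables judged relevant enter whatever their p-value, so the simulations describe the significance route and not the whole rule. This stands. That route names no variables, however, and does not switch the screen off.
- **The false predictors are not caused by screening as such.** Entering all candidates without a screen gives more of them (35 to 63%, against 30 to 49%). This stands. The number of candidates drives the rate, and the gain from the fix comes from a shorter list.
- **Missing a true predictor about two times in three is mainly low power.** A fixed five-covariate model finds it significant about as often. This stands, so the retention figure is no argument against the screen.
- **The model is peripheral.** No objective in the Aim section asks for predictors of events.

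A reader might also infer that the Barthel Index will be cut into a yes/no event, at a cost in power for the primary outcome. The protocol does not plan this. It speaks only of unnamed events and analyses the study variables by repeated measures ANOVA. It also mentions binary states that need no Barthel cut: death, progression to a terminal state and hospitalisation among the withdrawal criteria, and caregiver strain above a Zarit score of 17. Nor do the documents support the inference that the treatment comparison is biased, because that comparison does not pass through this model.

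**Conclusion.** The point holds as a modest, cheap improvement to a supplementary analysis. The significance route yields odds ratios and p-values that ignore how the covariates were chosen. At 72 patients and 50% events, with 8 to 15 independent null candidates, about 30 to 49% of trials would show at least one false predictor. A true log odds ratio of 0.40 would be reported at about 0.71 when it passes the screen.

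These sizes rest on an assumed event rate, number of candidates, independence and true effect, none of which the protocol gives. False predictors are likely, not certain. The comparison of the two groups is untouched.

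**What to change.** In the Data Analysis section:

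- Delete entry by bivariate significance.
- Name the binary event.
- List a short set of covariates chosen in advance on clinical grounds, for example arm, baseline Barthel, baseline mMRC, age and tumour type, and limit its length by the expected number of events.
- Keep and report every covariate whatever its p-value. This matters as much as the fixed list, because picking out only the significant results brings the inflation back (step 5 of the working).
- Use Firth penalised logistic regression if events are few.
- Label the model exploratory.

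A logistic model can stay; nothing here requires replacing it with linear regression on the Barthel.

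Five fixed covariates lower the chance of a false predictor to about 22% and remove the inflation due to selection. They do not cure low power for single predictors.

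The cost is a change of wording, with no new visits or instruments provided the listed covariates are recorded at baseline. The downside is that covariates outside the list are not explored in this model.

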## PROCEDURES AND DATA COLLECTION

**Evaluations and study plan:** Participants will be evaluated at three time points during the study: baseline evaluation (at the time of patient referral and before hospital discharge), follow-up evaluation (after 15 days), and final evaluation (one month after the initial evaluation, after the intervention).

The baseline evaluation will be conducted after recruitment and prior to randomization and group assignment. This initial evaluation includes recording independent variables and primary outcome variables, intervening variables, and several objective evaluation tests. After randomization, the corresponding intervention for each group will be carried out. Two subsequent evaluations, the follow-up evaluation and final evaluation, will be performed, during which participants will complete the same objective tests as in the initial evaluation. Results will be reported individually to those who requested to receive their information at the start of the study. All evaluations will be carried out by trained research personnel.

---

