**STATISTICAL ANALYSIS:**

The statistical analysis will be conducted on an intention-to-treat basis. Population characteristics will be presented as means and standard deviations for continuous variables and as frequency distributions for qualitative variables. To assess comparability at baseline between the two study groups, the Chi-Square test will be used for qualitative variables, and the Student's t-test will be used for comparing means between the two groups. The effect of the intervention on the study variables will be evaluated using a repeated measures ANOVA with two study factors (time \* group). Subgroup analyses will be conducted considering certain baseline evaluation variables and/or categories, such as age or initial score on the FACT scale. Hypothesis tests will have an alpha risk of 0.05 as the statistical significance threshold. The statistical software used will be SPSS, version 23.0.

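### Run in its classical form, the named three-visit repeated measures ANOVA drops a randomised patient who misses only the 15-day visit, discarding a measured 1-month Barthel despite the intention-to-treat statement

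*Protocol*

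**What the plan says.** The efficacy method is given twice in nearly the same words, under Data Analysis and under Statistical Analysis near the end of the protocol. Under Data Analysis: "The effect of the intervention on the study variables will be assessed using a repeated measures ANOVA with two study factors", namely time and group, in SPSS. Both sections commit to the same principle; in the later one, "The statistical analysis will be conducted on an intention-to-treat basis".

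Procedures and Data Collection supplies the levels of the time factor: "Participants will be evaluated at three time points during the study". These are baseline before discharge, 15 days, and 1 month after baseline, with the same tests each time. The primary outcome is the Barthel Index.

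The withdrawal criteria are death, progression to a terminal state, hospitalisation during home follow-up, and a final assessment that is not completed. A missed 15-day visit is not among them. The Sample size paragraph gives 40 per group and adds: "A follow-up loss rate of 10% has been estimated". It does not say which missing visit counts as a loss.

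**The concern.** Classical repeated measures ANOVA works on one complete row per patient. With three time levels, a patient with baseline and 1-month scores but no 15-day score is removed from the whole analysis. Under the protocol's own rules that patient has not been withdrawn and has provided the primary outcome at its final time point. The method then discards that value, although the same paragraph promises an intention-to-treat analysis.

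The situation is realistic. Patients enter with a Barthel between 20 and 55, and after discharge both follow-up visits take place at the university unit. The experimental arm has supervised home contact while the control arm has a booklet, so attendance could depend on both condition and arm. At stake are some power and the comparability of the arms, and both losses are avoidable because the outcome was observed.

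**Working it through.** **Inputs from the protocol (Randomization and Sample size paragraphs).**
- Error rates: "accepting an alpha risk of 0.05 and a beta risk of 0.2 in a bilateral contrast", so two-sided alpha 0.05 and power 0.80.
- Target: "40 subjects in each group are required to detect a difference of at least 5.8 units".
- Spread: "A common standard deviation of 8.7 is assumed".
- Loss: 10%. Allocation: 1:1.

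**Input not in the protocol (assumption).** The share of patients who have a 1-month Barthel but no 15-day visit, taken as 5% to 20%.

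**Step 1: reproduce the stated sample size.**
n per group = 2 × (1.960 + 0.842)² × (8.7/5.8)² = 35.3, rounded up to 36.
With 10% loss: 36/(1 − 0.10) = 40. This matches exactly. (Using the t distribution, 37 are needed, and 37/0.9 rounds up to 42, so the stated figure follows the normal approximation.)

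Hence 40 per group leaves 40 × 0.9 = 36 after the planned loss, which is just the number required.

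**Step 2: which patients the ANOVA itself removes.**

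| Visits attended | Withdrawn under the protocol's criteria? | In a complete-row ANOVA? |
|---|---|---|
| Baseline, 15 days, 1 month | No | Yes |
| Baseline, 1 month | No | No |
| Baseline, 15 days | Yes (final assessment incomplete) | No |
| Baseline only | Yes (final assessment incomplete) | No |

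Only the second row is a loss caused by the method alone.

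**Step 3: power if the 10% means a missing 1-month Barthel.**
Complete rows per group = 36 × (1 − m), where m is the share missing only day 15.
Power = Φ( (5.8/8.7) × √(n/2) − 1.960 ).
Example for m = 10%: n = 32.4; 0.667 × √16.2 = 2.683; 2.683 − 1.960 = 0.723; Φ = 76.5%.

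| m (assumed) | Complete rows per group | Measured 1-month scores discarded, both groups (72 × m) | Power, normal | Power, t-test | Randomised per group to keep 36, i.e. 36/(0.9 × (1 − m)) |
|---|---|---|---|---|---|
| 0% | 36.0 | 0 | 80.7% | 79.7% | 40 |
| 5% | 34.2 | about 4 | 78.7% | 77.5% | 43 |
| 10% | 32.4 | about 7 | 76.5% | 75.2% | 45 |
| 15% | 30.6 | about 11 | 74.1% | 72.7% | 48 |
| 20% | 28.8 | about 14 | 71.6% | 70.1% | 50 |

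**Step 4: power if the 10% already covers any missed visit.**
Complete rows = 40 × 0.9 = 36 per group and power is 80.7%, as planned. The patients in the second row of Step 2 are still excluded.

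These powers refer to the two-group comparison behind the sample size. Power of the time-by-group F test would need within-patient correlations, which the protocol does not give.

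**The case against.** The strongest reply is that no sentence in the protocol excludes incomplete patients. It names a method and a principle, and an analysis plan not shown here could impute missing scores before the ANOVA so that both hold. It is true that the exclusion follows from how the procedure works and is not written down. But the method the protocol itself fixes, followed as written, does not deliver the principle fixed beside it. The alternatives that Data Analysis lists for repeated measures (Snedecor's F and Friedman's test) need complete rows too. The possibility of a later repair does not make the named method a good choice.

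The time factor is also not spelled out level by level. If it held only baseline and 1 month, a missed 15-day visit would not matter. The three scheduled evaluations with identical tests make three levels the natural reading.

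Four stronger readings are tempting, and the protocol does not support them:

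- **That the ANOVA contradicts the 10% allowance.** The calculation gives 36/0.9 = 40 however the loss is defined, so no conflict with the allowance is shown.
- **That power falls below 80% outright.** This depends on how the 10% is defined and on a missed-visit rate that the protocol does not state. At 5% the fall is only 2 points.
- **That patients seen at 15 days but not at 1 month are lost because of the ANOVA.** They already meet a withdrawal criterion. Hospitalisation and terminal progression, both likely reasons for missing day 15, are withdrawal criteria as well.
- **That the effect estimate is biased by a known amount.** Bias is plausible if absence depends on condition and arm. Its size would need missingness rates by arm, visit-specific spreads and correlations, none of which is given.

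**Conclusion.** The point holds as a weakness in the choice of method. A classical time-by-group ANOVA over three visits discards the measured 1-month Barthel of a randomised patient who misses only the 15-day visit, which does not fit the declared intention-to-treat analysis. This rests on two readings: that all three visits enter the time factor, and that the ANOVA is run in its classical complete-row form.

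The cost in power is conditional. If the 10% loss means a missing 1-month outcome, power goes from about 80% to between 79% and 72% for an assumed 5% to 20% missing only day 15 (normal approximation). If the 10% covers any missed visit, planned power is kept and the conflict with intention-to-treat is what remains. Bias is possible but cannot be sized. The change is worth making because it is cheap and keeps outcomes already collected.

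**What to change.** In both Data Analysis and Statistical Analysis, replace the repeated measures ANOVA with a likelihood-based mixed model for repeated measures (SPSS MIXED) fitted to all observed Barthel values of all randomised patients. Name the 1-month group difference, adjusted for baseline, as the primary contrast. State that a missed 15-day visit does not remove a patient from the 1-month comparison. A baseline-adjusted ANCOVA of the 1-month Barthel would also keep these patients and is a reasonable simpler choice.

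In the Sample size paragraph, say that the 10% refers to a missing 1-month Barthel. With either replacement analysis the 40 per group then matches the analysis and leaves the required 36.

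The cost is wording in three places. The software stays the same, and no patients, visits or data are added. The one downside is that the mixed model relies on data being missing at random, which is a weaker assumption than complete-case ANOVA needs. Listing an incomplete final assessment as a withdrawal criterion also has to be reconciled with intention-to-treat, but that is a separate matter and this change does not depend on it.
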